**FIGURE 2 F2:**
[figure not shown]
Chronological data collection. PHQ-9, Patient Health Questionnaire; BDI-II, Beck Depression Inventory; GAD-7, Generalized Anxiety Disorder; AUDIT, Alcohol Use Disorders Identification Test; PGBQ, Pathological Gambling Brief Questionnaire; MULTICAGE-ICT, MULTICAGE-Information and Communications Technologies; GSES-12, General Self Efficacy Scale; CD-Risc-10, Connor–Davidson Resilience Scale; SOC-13, Sense of Coherence Scale; RSES, Rosenberg Self-Esteem Scale; PAM-13, Patient Activation Questionnaire; HLS-EUQ-16, Health Literacy Survey European Questionnaire; BFI-10, Big Five Inventory; EQ-5D, European Quality of Life-5 Dimensions Questionnaire; MEDAS, Mediterranean Diet Adherence Screener; PSQI, Pittsburgh Sleep Quality Index; IPAQ-SF, International Physical Activity Questionnaire-Short Form.

### 2.6. Measures

An evaluation will be carried out at baseline with further assessments five and ten years following the end of the baseline assessment. In this study, we will use valid instruments whose psychometric properties have been tested on the Spanish population to collect data; the validity and reliability of the questionnaires are reported in Table 3.

**TABLE 3 T3:** Instruments used in the study.

	Instrument	Developed by	Translated by	Item number	Range of score	Higher scores mean	Reliability developer	Translator
Primary outcomes	PHQ-9	Kroenke and Spitzer (70)	Muñoz-Navarro et al. (71)	9 (4-point Likert 0-3)	0–27	Depression ↑	α = 0.89	α = 0.80
	BDI-II	Beck et al. (72)	Sanz et al. (73)	21 (4-point Likert 0-3)	0–63	Depression ↑	α = 0.91	α = 0.87
	GAD-7	Spitzer et al. (74)	García-Campayo et al. (75)	7 (4-point Likert 0-3)	0–21	Anxiety ↑	α = 0.92	α = 0.93
	AUDIT	Saunders et al. (76)		10 (5-point Likert 0-4)	0–40	Alcohol problem↑	α = 0.93	
	PGBQ	Fernández-Montalvo et al. (77)		4 (Dichotomous 0-1)	0–4	Gambling addiction ↑	α = 0.95	
	MULTICAGE -ICT	Pedrero Pérez et al. (51)		20 (Dichotomous 0-1)	0–4 (Each factor)	ICT compulsive behaviors ↑	α = 0.93	
	GSES-12	Bosscher et al. (78)	Herrero et al. (79)	12 (5-point Likert 1-5)	12–60	Self-efficacy ↑	α = 0.74	α = 0.69
Secondary outcomes	CD-Risc-10	Campbell-Sills and Stein (18)	Notario-Pacheco et al. (80)	10 (5-point Likert 0-4)	0–40	Resilience ↑	α = 0.85	α = 0.85
	SOC-13	Antonovsky (19)	Moreno et al. (81)	13 (7-point Likert 1-7)	13–91	Sense of coherence ↑	α = 0.91	α = 0.83
	RSES	Rosenberg (20)	Martín-Albo et al. (82)	10 (5-point Likert 1-5)	10–50	Self-esteem ↑	α = 0.77	α = 0.85
	PAM-13	Hibbard et al. (16)	Moreno-Chico et al. (83)	13 (4-point Likert 1-4)	13–52	Patient activation ↑	α = 0.87	α = 0.7
	HLS-EUQ16	Sørensen et al. (15)	Nolasco et al. (84)	16 (Dichotomous 0-1)	0–16	Health literacy ↑	α = 0.91	α = 0.98
	BFI-10	John et al. (21)	Benet-Martínez and John (37)	10 (5-point Likert 1-5)	2–10 (Each factor)	Extraversion, Agreeableness, Neuroticism Conscientiousness, Openness↑	α = 0.83	α = 0.78
	EQ-5D	The EuroQol Group et al. (85)	Badia et al. (86)	5 (3-point Likert 1-3)		Better quality of life ↓	ρ = 0.99	α = 0.78
	MEDAS-14	Schröder et al. (87)		14 (Dichotomous 0-1)	0–14	Adherence to the Mediterranean diet ↑	*k* = 0.43 *r* = 0.52	
	MEDAS-17	Schröder et al. (88)		17 (Dichotomous 0-1)	0–17	Adherence to the Mediterranean diet ↑	*k* = 0.41 *r* = 0.61	
	PSQI	Buysse et al. (89)	Royuela-Rico and Macías-Fernández (90)	19 (4-point Likert 0-3)	0–21	Sleep quality↓	α = 0.83	α = 0.81
	IPAQ-SF	Craig et al. (91)	Puig-Ribera et al. (92)	7 (days and minutes of activity)	MET-minutes/we	Physical activity ↑	ρ = 0.96	*k* = 0.70

↑, going up; ↓, going down; α, Cronbach’s alpha; ρ, Spearman’s rho; k, kappa test-retest reliability; PHQ, Patient Health Questionnaire; BDI, Beck Depression Inventory; GAD, Generalized Anxiety Disorder; AUDIT, Alcohol Use Disorders Identification Test; PGBQ, Pathological Gambling Brief Questionnaire; ICT, Information and Communications Technologies; GSES, General Self Efficacy Scale; CD-Risc, Connor–Davidson Resilience Scale; SOC, Sense of Coherence Scale; RSES, Rosenberg Self-Esteem Scale; PAM, Patient Activation Questionnaire; HLS-EUQ, Health Literacy Survey European Questionnaire; BFI-10, Big Five Inventory; EQ-5D, European Quality of Life-5 Dimensions Questionnaire; MEDAS, Mediterranean Diet Adherence Screener; PSQI, Pittsburgh Sleep Quality Index; IPAQ-SF, International Physical Activity Questionnaire-Short Form.

#### 2.6.1. Primary outcomes

The main variables will be severity of depression, severity of anxiety, and addictive behaviors.

##### 2.6.1.1. Depression

Depression will be assessed by Patient Health Questionnaire-9 and Beck Depression Inventory. The Patient Health Questionnaire-9 (PHQ-9, Spanish version) will be used to measure the degree of depression in the past 2 weeks (70). The severity levels include no depression (0–4), mild depression (5–9), moderate depression (10–14), moderately severe depression (15–19) and severe depression (20–27). The validated Spanish version has a Cronbach’s alpha value (α) of 0.80 (71). The Beck Depression Inventory-Second Edition (BDI-II, Spanish version) will be used to measure the severity of depression (72). The severity levels include minimal depression/no depression (0–13), mild depression (14–19), moderate depression (20–28), and severe depression (29–63). In its Spanish version, the Cronbach’s alpha coefficient is 0.87 (73).

##### 2.6.1.2. Anxiety

The Generalized Anxiety Disorder-7 (GAD-7, Spanish version) will be used to measure anxiety level. Each item describes one of the typical symptoms of generalized anxiety disorders experienced over the last 2 weeks (74). The severity levels in the original study include no anxiety (0–4), mild anxiety (5–9), moderate anxiety (10–14) and severe anxiety (15–21). The validated Spanish version has a Cronbach’s alpha value (α) of 0.93 (75).

##### 2.6.1.3. Alcohol consumption

The Alcohol Use Disorders Identification Test Form (AUDIT, Spanish version) will be used to screen for excessive alcohol consumption. It will act as a support in the evaluation and identification of excessive alcohol consumption as a cause of disease, dependence and consequences of harmful consumption (76). Alcohol consumption dependence levels include no dependence (0–7), low dependence (8–15), moderate dependence (16–19) and high dependence (20–40). The validated Spanish version has a Cronbach’s alpha value (a) of 0.93 (75).

##### 2.6.1.4. Pathological gambling

The Pathological Gambling Brief Questionnaire (PGBQ) will be used to assess the psychometric behavior with respect to gambling addictions in the general population (77). A score ≥ 2 indicates possible gambling addiction problems, with a maximum score of 4. In its Spanish version, the Cronbach’s alpha coefficient is 0.95 (77).

##### 2.6.1.5. Pathological use of information and communication technologies

The MULTICAGE-ICT Questionnaire will be used to Assess problems related to the use of the Internet, mobile phones, video games, instant messaging, and social networks (51). Composed of 20 total items distributed in 5 scales (internet; mobile phone; video games; instant messaging; social networks). In each scale, item 1, the estimation of excess in temporary dedication; item 2, the estimation of significant others; item 3, the difficulty of not performing the behavior; item 4, the difficulties in voluntarily interrupting the behavior. Higher scores indicate higher use/abuse of Information and Communications Technologies (ICT). The validated Spanish version has a Cronbach’s alpha value (α) of 0.93 (51).

#### 2.6.2. Secondary outcomes

##### 2.6.2.1. Sociodemographic and clinical data

Sociodemographic information, including age, sex, marital status, education, socioeconomic status, and family sustainability, will also be obtained through an *ad hoc* questionnaire prepared by the research team. Health-related characteristics will include physical and psychological comorbidities. These data will be collected from the electronic medical record and will be included in the database following the definitions of diseases according to the International Classification of Primary Care (3rd edition). In addition, the physical examination will obtain anthropometric measurements (weight, height, and waist circumference). The analytical determination will complement the diagnosis of comorbidities with chronic diseases. In all patients, the concentrations of glucose (mg/dL), cholesterol, triglycerides, glycosylated hemoglobin (%), Thyroid-Stimulating Hormone (μIU/mL), complete blood count, iron metabolism, and calcifediol will be obtained.

##### 2.6.2.2. Self-efficacy

The General Self Efficacy Scale (GSES-12, Spanish version) will be used to evaluate perceived global self-efficacy as feeling confident in one’s abilities to adequately handle certain stressors in life (78). The final score on the questionnaire is the sum of the responses obtained on each item (range 12–60) and higher scores indicate higher levels of self-efficacy. The validated Spanish version has a Cronbach’s alpha value (α) of 0.69 (79).

##### 2.6.2.3. Resilience

The Connor–Davidson Resilience Scale (CD-Risc-10, Spanish version) will be used to evaluate resilience as the positive adaptation to circumstances of significant adversity such as misfortunes and tragic situations in life (18). The final score on the questionnaire is the sum of the responses obtained on each item (range 0–40), and higher scores indicate higher levels of resilience. The validated Spanish version has a Cronbach’s alpha value (α) of 0.85 (80).

##### 2.6.2.4. Sense of coherence

The Sense of Coherence Scale (SOC-13, Spanish version) will be used to measure sense of coherence in terms of the personal disposition toward the values of vital experiences. It also measures understandability, manageability and meaning (19). Higher scores (after flipping the flipped items) (range 13–91) indicate a greater sense of coherence. The validated Spanish version has a Cronbach’s alpha value (α) of 0.83 (81).

##### 2.6.2.5. Self-esteem

The Rosenberg Self-Esteem Scale (RSES, Spanish version) will be used to assess self-esteem during the past 2 weeks (20). Self-esteem is defined as feelings toward oneself, which can be positive or negative, and is determined based on an evaluation of one’s own characteristics. Scores below 25 points are considered to reflect significant low self-esteem issues. The validated Spanish version has a Cronbach’s alpha value (α) of 0.85 (82).

##### 2.6.2.6. Patient activation

The Patient Activation Questionnaire (PAM-13, Spanish version) will be used to measure activation as the capacity and ability to manage one’s personal condition of his/her health and how competent he/she feels in taking on this role (16). The final score on the questionnaire is the sum of the responses obtained on each item (range 13–52) and higher scores indicate a higher level of patients’ activation in addressing their own health. We decided not to include the category “not applicable” to avoid misinterpretations. In its Spanish version, the Cronbach’s alpha coefficient is 0.7 (83).

##### 2.6.2.7. Health literacy

The Health Literacy Survey European Questionnaire (HLS-EU-Q16, Spanish version) will be used to measure the level of health literacy as knowledge of the population, motivation, and individual abilities to understand and make decisions related to the promotion and management of participants’ own health (15). The score of each subject will be obtained from the sum of the scores of the 16 items, transforming each one into a dichotomous response: very difficult and difficult = 0; easy and very easy = 1. The health literacy levels include an inadequate or problematic level (0–12) and a sufficient level (13–16). In its Spanish version, the Cronbach’s alpha coefficient is 0.98 (84).

##### 2.6.2.8. Personality characteristics

The Big Five Inventory-10 (BFI-10, Spanish version) will be used to examine personality characteristics (21). The questionnaire measures the 5 factors of personality from the five factors model (each factor entails two items). Extraversion (Extraverts engage actively with others to earn friendship, admiration, power, status, excitement, and romance; Introverts conserve their energy and do not work as hard to earn these social rewards). Agreeableness (High scores have a great deal of empathy and tend to get pleasure out of serving and taking care of others; Low scorers are often described as hostile, competitive, and antagonistic). Conscientiousness (High scorers are organized and determined; Low scorers are impulsive and easily side-tracked). Neuroticism (High scorers are more likely to react to a situation with fear, anger, sadness, and the like. Low scorers are more likely to brush off their misfortune and move on). Openness (High scorers tend to be creative, adventurous, and intellectual; Low scorers tend to be practical, conventional, and focused on concrete information). The validated Spanish version has a Cronbach’s alpha value (α) of 0.78 (37).

##### 2.6.2.9. Health-related quality of life

The European Quality of Life-5 Dimensions Questionnaire (EQ-5D, Spanish version) will be used to measure health-related quality of life. It will be used to calculate the quality-adjusted life year (QALY) during the monitoring period by adjusting the length of time affected by the health result in relation to the utility value (85). It contains five health dimensions (mobility, self-care, usual activities, pain/discomfort and anxiety/depression), and each of these has three levels (no problems, slight or moderate problems, and severe problems). Moreover, this questionnaire incorporates a Visual Analog Scale (VAS) which can be used as a quantitative measure of health outcome reflecting the patient’s own judgment. Patients mark the point on the vertical line that best reflects their assessment of their current global health status. In its Spanish version, the Cronbach’s alpha coefficient is 0.78 (86).

##### 2.6.2.10. Diet adherence

The Mediterranean Diet Adherence Screener (MEDAS) was developed within the Mediterranean diet (PREDIMED) study group. We will also evaluate the adherence to the Mediterranean diet, assessed with the MEDAS (14 items) (87) and MEDAS plus (17 items) (88) questionnaires. Both questionnaires share many of their items, including food and consumption habits: the use of olive oil as the main source of cooking fat, preference for white meat over red meat, servings of vegetables, portions of fruit, red meat or sausages, servings of animal fat, sugar-sweetened beverages, red wine, legumes, fish, commercial pastries and dressing foods with a traditional sauce made of tomatoes, garlic, onion or leeks sautéed in olive oil. However, the stricter values of some items and the inclusion of some additional items in the 17-point version is an attempt to better reflect the possible caloric restriction that should be applied to the Mediterranean diet pattern when the goal is to lose weight. The MEDAS-14 levels include low adherence (0–8) and good adherence (9–14) (87). The MEDAS-17 levels include low adherence (0–7), medium adherence (8–10) and high adherence (11–17) (88). The construct validity of MEDAS was determined by analyzing the correlations of the MEDAS score with dietary intake reported on the food frequency questionnaire (FFQ) with a moderate correlation and moderate mean agreement for both versions (*r* = 0.52 and *k* = 0.43 for the 14-item version and *r* = 0.61 and *k* = 0.41 for the 17-item version) (87, 88).

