
Furthermore, the onset and persistence of affective disorders has been associated with specific lifestyle characteristics (e.g., poor-quality diet, sleep disturbances, and sedentary lifestyle) (41–43). Therefore, some healthy habits (e.g., good nutrition, quality sleep, sufficient physical activity) are associated with lower levels of depression and anxiety (44, 45). In particular, improving physical activity has a moderate to large effect on improving depressive symptoms (46). Additionally, depression severity and current depression diagnosis are associated with unhealthy dietary intake and poorer food quality (47). Moreover, sleep disturbances increase the risk of suicidal behavior in depressed patients (48). Furthermore, addictive behaviors (e.g., tobacco use, harmful use of alcohol, substance abuse, and compulsive use of the Information and Communications Technologies (ICT) can coincide with, contribute to, or result from mental disorders such as depression or anxiety (49–51). Current evidence suggests the high probability of exacerbation of anxious or depressive disorders when they coexist with chronic comorbidities (52). Several studies have found that people with chronic diseases have a higher risk of developing mental disorders such as depression or anxiety (52–54). Simultaneously, people diagnosed with a mental health disorder are more likely to have chronic physical conditions than a person without a mental health diagnosis (52, 55). Moreover, a prospective cohort study of community individuals with a follow-up after 11 years indicated that the increase in depressive symptoms over time was associated with higher mortality rates (56).

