### 2.7. Data analysis

Baseline analysis of the results: Descriptive analysis of all variables (percentage and confidence interval for qualitative variables; means and standard deviation for parametric quantitative variables or median and interquartile range for non-parametric quantitative variables) and univariate analysis (we will use the T-Student for parametric quantitative variable, Mann-Whitney U for non-parametric quantitative variables, and the Chi-Square test for qualitative variables) to evaluate the differences between the patients who have some of the most prevalent affective-emotional problems in primary care (anxiety, depression) compared with those who do not. Statistical analyses will be chosen based on the size of the sample (parametric or non-parametric tests). To compare the two groups, missing data will be assessed and the need to use an intention-to-treat (ITT) analysis and a multiple imputation (MI) technique to handle missing data will be assessed.

To answer the main objective, we will use a multiple linear regression model. To do this, each main variable, the PHQ-9 score, BDI-II, GAD-7, PGBQ, AUDIT, and MULTICAGE-ICT, will be used as a continuous variable. Multiple linear regression will be performed using a stepwise method to obtain a better fit result to the statistical analysis. This stepwise regression simply will repeat the multiple regression, each time removing the least correlated variable. Only the significant variables obtained in the bivariate analysis will be entered into the regression model.

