Finally, mediation/moderation analyses will be carried out to analyze whether psychological constructs participate as a mediator or as a moderator in the association of lifestyles (exposure) and anxiety, depression and/or addictions (outcome). The PROCESS analytical tool developed by Hayes will be used to assess mediation/moderation. These analyses were based on multiple linear regression path analysis (93). Bootstrap resampling (10.000 samples) will be used to estimate 95% confidence intervals. Given that heteroscedasticity is common in cross-sectional data, all analyses will include a correction for heteroscedasticity (HC0) (94). The Johnson-Neyman technique will be used to compute the range of significance and simple slopes for the interaction analyses (93). We will report unstandardized regression coefficients; all analyses will be two-tailed and used conventional significance thresholds (α = 0.05). Data collection and statistical analysis will be performed using Excel software, SPSS software (version 25.0) (95) and the statistical software environment R (version 3.6.2) (96).

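### The diet scores contain a red-wine item and AUDIT is an outcome, so total and direct diet-AUDIT effects partly reflect alcohol measured on both sides

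*Protocol article*

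**What the plan says.** Five statements in the protocol article combine here.

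- **Diet measure.** Section 2.6.2.10 says that adherence is "assessed with the MEDAS (14 items) (87) and MEDAS plus (17 items) (88) questionnaires". Its list of items common to both versions includes "sugar-sweetened beverages, red wine, legumes, fish". Table 3 in section 2.6 gives the format of the shorter version as "14 (Dichotomous 0-1" per item. The 17-item version has the same format, so the wine item is one point of 14 or of 17.
- **Diet as a lifestyle.** The Introduction speaks of "specific lifestyle characteristics (e.g., poor-quality diet, sleep disturbances, and sedentary lifestyle". The Discussion repeats diet in its list of lifestyles and adds alcohol consumption to that list.
- **Alcohol measure.** Section 2.6.1.3 says that AUDIT "will be used to screen for excessive alcohol consumption". It also covers dependence and the consequences of harmful use.
- **AUDIT as an outcome.** Section 2.7 states that "PGBQ, AUDIT, and MULTICAGE-ICT, will be used as a continuous variable".
- **The pairing.** The mediation and moderation models in section 2.7 study psychological constructs "in the association of lifestyles (exposure) and anxiety, depression and/or addictions (outcome").

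The article does not say that the wine item is removed when diet is paired with AUDIT.

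**The concern.** When a score used as exposure contains an item on the same behaviour that the outcome measures, part of their association is built in. If wine drinking earns a diet point, better adherence goes mechanically with a higher AUDIT score, against the expected protective direction. If wine drinking costs a point, the same artefact looks like protection. The article does not give the scoring direction, so the sign cannot be settled from it.

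A larger sample does not remove the artefact; it makes it more likely to reach significance. At stake is the reading of one exposure-outcome pair: whether a reported diet-alcohol association says anything about diet other than wine. The depression, anxiety, gambling and ICT outcomes do not share this item.

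**Working it through.** The plan gives no figure for this association, so there is none to reproduce. The check sizes the overlap.

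**Inputs from the article.** Items are scored 0/1 (Table 3). Tests are two-sided at 0.05 (section 2.7). The required sample is 290 (section 2.4), while Table 2 totals 395. Both sizes are used, only to scale the result.

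**Assumed inputs, not in the article.** Share scoring the wine item, p: 10-30%. Correlation of the wine item with AUDIT, r_W: 0.2-0.5. SD of the MEDAS-14 total: 1.5-2.5 points. The other 13 items are unrelated to AUDIT and to the wine item.

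**Step 1. Weight of the item.** 1/14 = 7.1% of the maximum score, or 1/17 = 5.9%.

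**Step 2. Induced correlation.** Write the total as the wine item W plus the rest. If the rest is unrelated to AUDIT, then

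r(total, AUDIT) = r_W × SD(W) / SD(total), with SD(W) = √(p(1−p)).

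- Low: 0.2 × √(0.1×0.9) / 2.5 = 0.2 × 0.300 / 2.5 = 0.024
- Middle (p = 20%, r_W = 0.3, SD = 2.0): 0.3 × 0.400 / 2.0 = 0.060
- High: 0.5 × √(0.3×0.7) / 1.5 = 0.5 × 0.458 / 1.5 = 0.153

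Raising p to 35% moves the top only to 0.5 × 0.477 / 1.5 = 0.159.

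**Step 3. Critical value.** |r| = t / √(n−2+t²), with t the 97.5% point on n−2 degrees of freedom. This gives 0.115 at n=290 and 0.099 at n=395.

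**Step 4. Chance of a significant correlation with no true diet effect** (Fisher z, mean atanh(r) × √(n−3), two-sided 0.05):

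| Case | Induced r | n=290 | n=395 |
|---|---|---|---|
| Low | 0.024 | 7% | 8% |
| Middle | 0.060 | 17% | 22% |
| High | 0.153 | 74% | 86% |

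The nominal rate is 5%.

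**Step 5. Masking of a real association.** Suppose the other 13 items correlate 0.10 with AUDIT in the direction opposite to the wine item. At middle values the SD of the other items is √(2.0² − 0.4²) = 1.96. The total-score correlation is (0.3×0.4 − 0.10×1.96)/2.0 = −0.038, so an association of 0.10 shrinks to about 0.04.

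**Step 6. Which parts of the model are affected.** The wine item adds a term to the diet-AUDIT path. If that term is the same at every level of the construct, it shifts the direct effect and every simple slope but does not create an interaction. It also does not enter the path from construct to outcome. A simulation with HC0 errors used p 20-35%, r_W 0.3-0.5 and SD 1.8-2.0, at both sample sizes. The interaction test rejected 5.4-6.3% of the time, and the mean indirect effect was −0.040 against a true −0.040. The direct effect was falsely significant 17-77% of the time.

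**The case against.** **The pairing is inferred.** Section 2.7 names neither MEDAS nor AUDIT in the exposure-outcome sentence, and does not say whether diet enters as a total or as adherence bands. This is fair, and the formula applies only to the continuous total. But MEDAS is the only diet instrument, diet is called a lifestyle twice, and AUDIT is one of the listed addiction outcomes. Bands cut from the same totals would still contain the wine item.

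**The hypothesis concerns mediation and moderation, not the diet-AUDIT correlation.** This stands and narrows the point. A reader might infer that the overlap invalidates the moderation or mediation tests. It does not, provided the wine-AUDIT link is the same across construct levels. What remains affected is the total and direct effect, and the slopes and regions reported with it.

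**The main-objective regression.** A reader might also infer that the artefact carries diet into the AUDIT model of the main objective. That is weakly supported. The only group comparison that section 2.7 describes is between people with and without anxiety or depression, and a wine-AUDIT link would not help diet pass such a screen. The main hypothesis concerns psychological constructs, so diet would be a covariate there.

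**Size.** Every input to the size is assumed. A steep loss of power can be produced: with a true correlation of −0.15 and an induced +0.10, power at n=290 falls from 73% to about 14%. But 0.10 is well above the middle value; at 0.06 the fall is to 33%. The article states no expected diet-AUDIT correlation, so neither figure should be used as a headline.

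**Left to an analysis plan.** Item-level derivations often are. Here, however, the article itself fixes the instrument, its content, the roles and the model, and the overlap follows from those choices.

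**Conclusion.** The point holds in a limited form. As written, the plan puts alcohol intake into both the diet exposure and the AUDIT outcome. The total and direct diet-AUDIT effects, the simple slopes and the Johnson-Neyman regions are therefore partly built in. The interaction and indirect-effect tests are largely unaffected, on the condition in step 6.

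The bias is probably small to moderate: an induced correlation of about 0.06 at middle assumptions, within a range of about 0.02 to 0.15. It matters because the smallest correlation that reaches significance at these sample sizes, 0.115 or 0.099, is of the same order. The overlap is one dichotomous item against a ten-item scale that also covers dependence and harm. Saying that alcohol is simply regressed on itself would therefore go further than the article supports. The sign is unknown.

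**What to change.** Add one sentence to section 2.7: models that pair diet with AUDIT use MEDAS without the red-wine item (range 0-13 for the 14-item version, 0-16 for the 17-item version), the full-score result is reported alongside, and the full score is kept for all other outcomes.

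The wine-free score is one derived variable per version, from items already collected. With the item removed, its mechanical contribution is zero by construction. The small cost is that the adherence cut-offs in section 2.6.2.10 do not apply to the shortened score. A linear model using the score itself does not need them. Making the full score the main result and the wine-free score the sensitivity analysis would also be defensible, provided both are reported and the choice is fixed beforehand.
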